## Abstract

**Background:**

Internet-based self-management (IBSM) support cost-effectively improves asthma control, asthma related quality of life, number of symptom-free days, and lung function in patients with mild to moderate persistent asthma. The current challenge is to implement IBSM in clinical practice.

**Methods/design:**

This study is a three-arm cluster randomized trial with a cluster pre-randomisation design and 12 months follow-up per practice comparing the following three IBSM implementation strategies: minimum strategy (MS): dissemination of the IBSM program; intermediate strategy (IS): MS + start-up support for professionals (*i.e.*, support in selection of the appropriate population and training of professionals); and extended strategy (ES): IS + additional training and ongoing support for professionals. Because the implementation strategies (interventions) are primarily targeted at general practices, randomisation will occur at practice level.

In this study, we aim to evaluate 14 primary care practices per strategy in the Leiden-The Hague region, involving 140 patients per arm. Patients aged 18 to 50 years, with a physician diagnosis of asthma, prescription of inhaled corticosteroids, and/or montelukast for ≥3 months in the previous year are eligible to participate. Primary outcome measures are the proportion of referred patients that participate in IBSM, and the proportion of patients that have clinically relevant improvement in the asthma-related quality of life. The secondary effect measures are clinical outcomes (asthma control, lung function, usage of airway treatment, and presence of exacerbations); self-management related outcomes (health education impact*,* medication adherence, and illness perceptions); and patient utilities. Process measures are the proportion of practices that participate in IBSM and adherence of professionals to implementation strategies. Cost-effective measurements are medical costs and healthcare consumption. Follow-up is six months per patient.

**Discussion:**

This study provides insight in the amount of support that is required by general practices for cost-effective implementation of IBSM. Additionally, design and results can be beneficial for implementation of other self-management initiatives in clinical practice.

**Trial registration:**

the Netherlands National Trial Register NTR2970

## Background

Asthma is a common chronic inflammatory disease of the airways, typically characterized by symptoms such as wheeze, shortness of breath, and coughing
[1]. Despite the wide availability of effective therapy, long-term management of asthma falls for short of the goals set in guidelines
[2], and many patients do experience a profound burden of disease
[3].

Self-management is an essential component in the proactive management of asthma
[1,4] because it helps patients to reach their treatment goals and enables patients to manage symptoms, treatment, physical and psychosocial consequences, and lifestyle changes inherent in living with a chronic condition
[5]. However, the uptake of self-management in clinical practice may be hampered because easy-use tools that enhance sustained uptake of action plan usage by patients are lacking in today’s practice
[6], and patients can experience a lack of ownership of these action plans
[7]. Not surprisingly, a minority of general practices provide patients with written action plans
[8,9].

Internet technology is increasingly being seen as an appealing tool for self-management for patients with chronic disease
[10-12]. Telehealth care in asthma is defined as healthcare being delivered from a distance, facilitated electronically, and involving the exchange of information through the personalized interaction between a healthcare professional using their skills, judgment, and the patient providing information
[13]. Telehealth care may overcome barriers towards optimal care in patients with mild to moderate asthma
[14]. More specifically, internet technology can be employed for ongoing individualized management of the patient
[15].

Internet-based self-management (IBSM) support in asthma consists of the following components: internet-based asthma monitoring, internet-based goal setting, decision support with a treatment plan, online medical review, tailored online information, and communication with a healthcare provider. Recently, we have shown that such IBSM can improve asthma-related quality of life, asthma control, the number of symptom-free days, and lung function in patients with mild to moderate persistent asthma, as compared to usual care
[16]. In a cost-utility analysis
[17], it was demonstrated that IBSM support can be as effective as current asthma care with regard to quality of life in terms of patient utilities, and costs are similar over a one-year period.

Therefore, the current challenge is to implement IBSM support in routine asthma management within primary care. Patients that are most likely to be willing to participate and benefit from (internet-based) self-management are those with partially controlled or uncontrolled asthma
[18-20]. These patients constitute about two-thirds of the asthma population in primary care
[8].

A structured implementation strategy is needed to incorporate IBSM in current clinical practice and subsequently into a patient’s daily life. Implementation strategies for IBSM, consisting of several components (so-called ‘multi-faceted implementation strategy’) are suggested to be more effective in changing current clinical practices
[21]. In addition, tailoring the implementation strategy to barriers and facilitators experienced by the target group—patients with asthma, practice nurses (PNs), and general practitioners (GPs)—is recommended
[22-24]. Such barriers can be identified at different levels of healthcare system
[25]: innovation, the individual patient (*i.e.*, illness perceptions), professional level, societal context (opinion of colleagues), organisational context (organisation of care process), and economic and political contexts.

Prior to this project, we conducted focus groups and interviews with patients and professionals for exploring barriers and facilitators for usage of IBSM in primary care
[26]. These barriers were identified at patient and professional/organizational level. Main barriers at the patient level were unawareness of their level of asthma control and subsequent possibility for improvement, and patients often do not perceive asthma as a chronic condition and experience difficulties of integrating self-management activities into daily life. Main barriers at the professional level (PN, GP) and organizational level were unawareness of the level of asthma control of patients, lack of structure of asthma care, and lack of structure of routine asthma consultations within general practice and lack of time. Consequently, we developed three implementation strategies (the strategies will be described in more detail below):

1. Minimum strategy (MS): dissemination of the IBSM program.

2. Intermediate strategy (IS): MS + start-up support for professionals (*i.e.*, support in selection of the appropriate population and training of professionals).

3. Extended strategy (ES): IS + additional training and ongoing support for professionals.

In summary, the MS strategy has not been tailored to previously identified barriers and corresponds with commonly used implementation strategies (*i.e.*, dissemination of the innovation only). This is in contrast with the IS strategy, which specifically have been developed for addressing previous identified barriers. The ES strategy is the most extensive and time-intensive strategy. Currently, there are only sparse data on the effectiveness and cost-effectiveness of implementation strategies for IBSM in primary care. This information is particularly important for the time-intensive implementation interventions, such as selection of the appropriate population, professional training, and ongoing support for professionals in IBSM support.

### Hypotheses

To evaluate the impact of these three different implementation strategies for IBSM in current clinical practice, we have proposed four hypotheses, which are constructed to compare the effect of tailoring implementation strategies to identified barriers (IS and ES) versus a commonly used, non-tailored strategy (MS):

1. More general practices will participate in IBSM in the IS or ES strategy as compared with the MS strategy;

2. The proportion of referred patients who participate in the IBSM program in the ES or IS strategy will be greater as compared with the MS strategy;

3. The proportion of referred patients who participate in the IBSM program in the ES or IS strategy will be greater as compared to the MS strategy;

4. The ES and the IS strategy will be more cost-effective as compared to the MS strategy.

### Objectives

The objectives of this study are to investigate the effectiveness and cost-effectiveness of a MS strategy, as compared to an IS strategy and an ES strategy in a three-arm, cluster randomized trial. Because these different implementation strategies have a sequence of effects, the evaluation is aimed to assess to what extent: practices participate in IBSM; IBSM improves asthma related quality of life; patients participate in IBSM; and the various implementation strategies are cost-effective.

## Methods

### Study design

This study is a three-arm, cluster randomized trial with a cluster pre-randomisation design
[7] (Figure 
1). Because the implementation strategies are primarily targeted at general practices, randomisation will occur at practice level (CONSORT guidelines for cluster trials, Table 
1[27]). Prior to obtaining informed consent from GPs and patients, practices will be allocated to one of the strategies. Follow-up per practice is 12 months. At patient level, follow-up duration is six months. In the ES and IS strategies, individual patient outcomes will be evaluated at baseline (first visit of a patient to the general practice for instruction on IBSM), and three and six months after a patient’s start with IBSM. Individual patient outcomes in the MS strategy will be evaluated at six months (end-point evaluation) after a patient’s start with IBSM.

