#### Endpoint evaluation

Patients in practices randomized to the MS strategy, and those patients in the IS and ES strategy not willing to participate in IBSM support, will only be approached for an endpoint evaluation at six months after their start with PatientCoach.

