#### PatientCoach

Patientcoach.nl is a generic web-based system that supports self-management of patients with a chronic condition. It includes modules for coaching, personalized information (*i.e.*, inhalation technique), self-monitoring, reminders, treatment plan, (motivational) feedback, e-consultations and a forum. PatientCoach has been developed by the Leiden University Medical Centre (LUMC)
[16]. The program includes options for weekly assessment of the level of asthma control
[28,29] and a quarterly-assessment of asthma-related quality of life
[30]. Furthermore, it offers tools for professionals and patients, to help them to incorporate IBSM respectively into routine asthma care and daily life, such as: reminder options for home monitoring by ACQ and lung function; reminder options for routine consultations (*i.e.*, digital agenda); reminder options (*i.e.*, a general agenda) for regional educative sessions on asthma, *i.e.*, hosted by the patient association of the Netherlands Asthma association; and a forum for professionals.

PatientCoach contains a research module that consists of electronic versions of questionnaires for assessment of quality of life
[31], health education impact
[31], self-reported medication adherence
[32], illness perceptions
[33] and costs
[34].

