#### Measurements and outcomes

Primary outcome measures are the proportion of referred patients that participate in IBSM and the proportion of patients that have clinically relevant improvement in the asthma-related quality of life as measured by the Asthma Quality of Life Questionnaire
[30]. Patient usage of IBSM is based on monitoring of the level of asthma control using the Asthma Control Questionnaire
[28,29]; monitoring of ACQ during two out of three months ACQ-monitoring compliance.

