**Quality of life/patient utilities**			
Asthma related quality of life (AQLQ)	A	A	A,N
Utilities: (EQ-5D)	X	X	A,N

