#### Analysis of clinical data

The number of patients with a clinically relevant improvement in asthma-related quality of life is based on a minimal clinical importance of difference (MCID) of 0.5 for the AQLQ
[30].Patient utilities: asthma symptom utilities are obtained from the AQLQ
[42]; indirect utilities from the general public are obtained using the EQ-5D
[31,43]. This allows the calculation of quality-adjusted life years (Qalys). In the base case analysis, Qalys are estimated using societal utilities obtained using the Dutch EQ-5D tariff
[45]. For sensitivity analyses, Qalys are estimated using a VAS (transformed using a power transformation). Data on healthcare provider utilization and other related costs provide input for calculation of the contract price that GPs will have to negotiate for this improved service. Ideally, this is in the form of a primary care diagnosis and treatment standard fee.

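### The text and Table 4 disagree on whether minimum-strategy (MS) patients have a baseline AQLQ, and this decides whether one primary outcome can be compared with MS

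*Protocol article*

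**What the plan says.** All references are to the protocol article.

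- **Outcome.** Measurements and outcomes names as a primary outcome "the proportion of patients that have clinically relevant improvement in the asthma-related quality of life", measured with the AQLQ. Analysis of clinical data adds that the count of improved patients "is based on a minimal clinical importance of difference (MCID) of 0.5 for the AQLQ".
- **Schedule in the text.** Study design places IS and ES assessments at baseline, three and six months. For MS it says "Individual patient outcomes in the MS strategy will be evaluated at six months (end-point evaluation". Endpoint evaluation states that MS patients, and IS and ES patients unwilling to use the programme, "will only be approached for an endpoint evaluation at six months".
- **Schedule in Table 4.** The row "Asthma related quality of life (AQLQ") carries code A at 0 months, A at 3 months, and A and N at six months. The key defines A as all strategies, X as IS and ES only, and N as non-participating practices.
- **The software.** The PatientCoach section lists "a quarterly-assessment of asthma-related quality of life" among the programme's options, with no limit by strategy.
- **Hypotheses.** Hypotheses 2 and 3 both concern the share of referred patients who participate. Hypothesis 3 ends "in the ES or IS strategy will be greater as compared to the MS strategy"; hypothesis 2 differs only in one preposition.

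**The concern.** Improvement is a within-patient change. An arm measured once yields a level but no change, and the random-effects model in the Analysis section cannot supply a baseline that was never collected. MS is the comparator in every stated hypothesis, so a missing MS baseline would remove both planned contrasts on one of the two primary outcomes.

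The conflict is about data collection, so an analysis plan cannot repair it later. Table 1 reports patient recruitment as ongoing, and a baseline that is missed cannot be recovered. A team that followed the text and a team that followed Table 4 would collect different data in MS.

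**Working it through.** **1. The two schedules for the AQLQ, side by side**

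| Group | Study design and Endpoint evaluation | Table 4 | Change of 0.5 computable? |
|---|---|---|---|
| IS and ES users | 0, 3, 6 months | 0, 3, 6 months (A) | Yes under both |
| MS patients | 6 months only | 0, 3, 6 months (A) | No under the text, yes under Table 4 |
| IS and ES decliners | 6 months only | No code | No under the text, undefined under Table 4 |

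**2. Contrasts that depend on the choice.** Two contrasts involve MS: IS vs MS and ES vs MS. Under the text 0 of 2 can be computed on this outcome; under Table 4, 2 of 2.

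**3. Patients affected under the text's schedule.** Sample size calculation gives 14 practices × 10 patients = 140 per strategy, and 3 × 140 = 420 in total. The MS share is 140/420, one third.

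**4. Does the sample size depend on the AQLQ baseline?** It is based on participation. Inputs from that section are 5% in MS, an increase of 25% (read here as percentage points, so 30%), alpha 0.05 (two-sided assumed), power 0.80, intra-cluster correlation 0.25 and 10 patients per practice.

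- Two proportions with continuity correction: n = 43 per arm before clustering. A two-sided alpha of 0.025 without the correction also gives 43.
- Design effect: 1 + (10 − 1) × 0.25 = 3.25.
- 43 × 3.25 = 139.75, hence 14 practices of 10, or 140 per arm and 420 in total.

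The stated figure is reproduced and no AQLQ quantity enters it.

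**5. Decliners.** The Analysis section is intention-to-treat. Under Patients, those who decline are asked to consent only to an endpoint evaluation at six months. Table 4's N refers to practices that do not participate, so it does not describe a declining patient inside a participating practice. Neither source gives these patients a first score. Endpoint evaluation also counts their six months from a start with PatientCoach that decliners never make.

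**6. Hypotheses against objectives.** Objectives lists four items: practice participation, quality of life, patient participation and cost-effectiveness. Hypotheses lists practice participation, patient participation, patient participation again, and cost-effectiveness. Quality of life is the one objective without a hypothesis.

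**The case against.** The strongest reply is that Table 4 settles the matter. It keeps a separate code X for items limited to IS and ES, so code A on the AQLQ row looks deliberate. The PatientCoach section fits this: the AQLQ is part of the programme itself, whereas health education impact, adherence, illness perceptions and costs sit in the research module. The endpoint-only rule for MS may have been meant for that research evaluation.

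This stands as far as it goes. A reader might infer from the text alone that the comparator has no baseline and that the outcome cannot be computed. The documents do not support that flat statement, because Table 4 schedules the baseline.

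Table 4 cannot simply be presumed to prevail, however. Two sections state the restriction, one of them with an explicit exclusive. The Discussion gives a reason for it: research activity is kept minimal in MS because it may itself stimulate uptake. Table 4 also leaves MS out of the EQ-5D at 0 and 3 months. Figure 1, which may show the schedule, is not available here.

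Two further inferences go too far:

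- **Case mix.** A reader might conclude that all case-mix adjustment would be lost. Table 4 lists demographic characteristics in all strategies at 0 months, and practice characteristics are also recorded. Only adjustment for baseline AQLQ would go.
- **Hypothesis 3.** The duplication is an editorial slip. Quality of life is still stated as an objective and as a primary outcome.

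**Conclusion.** The point holds as an internal contradiction, not as a proven absence of data. Study design and Endpoint evaluation give MS one assessment at six months; Table 4 gives it three. Under the first, all 140 planned MS patients lack the score that the responder definition needs and both contrasts with MS are lost on this outcome. Under the second, both are available. This rests on reading improvement as a within-patient gain of at least 0.5, which is what the stated outcome and threshold imply.

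Two smaller points go with it. The responder proportion is undefined under intention-to-treat for IS and ES patients who decline, whichever schedule is followed. Hypothesis 3 duplicates hypothesis 2; that it was meant for quality of life is an inference from the list of objectives. The participation outcome and its sample size are not touched.

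**What to change.** 1. **Reconcile the schedule.** Amend Study design and Endpoint evaluation to match Table 4, stating that the AQLQ is collected at baseline and at three and six months in MS as well as in IS and ES. Use the baseline already defined for IS and ES, the instruction visit, and make the questionnaire a scheduled item there. Leaving it to the optional quarterly module is risky, since Sample size calculation expects only 5% frequent use in MS. The cost is protocol wording and a web questionnaire that the programme already contains. The downside is slightly more research contact in MS, which the Discussion wants minimised; this should be acknowledged.

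2. **Settle the decliners.** There are two options:
   - Take a baseline AQLQ at the consultation where consent is sought. This extends the consent described under Patients, which now covers only the six-month evaluation.
   - State that the AQLQ-improvement analysis is restricted to patients with a baseline. This costs no data collection, but the analysed set is then selected after randomisation by a decision that the strategies aim to influence, and the protocol should say so.

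   Table 4 needs a code for declining patients either way.

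3. **Correct hypothesis 3.** If the inference from Objectives is right, reword it as the comparison of AQLQ improvement in IS or ES with MS. This is an editorial change only.

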**Figure 1 F1:**
[figure not shown]
Study design.

**Table 1 T1:** **Consort checklist**[27]

**Item**	**Standard Checklist item**	
**Title**	Identification of study as randomised	Implementation strategies of internet-based asthma self-management support in usual care. Study protocol of the IMPASSE study - a cluster randomized trial
**Trial design**	Description of the trial design (e.g., parallel, cluster, non-inferiority)	Cluster-randomized trial with a cluster pre-randomization design.
**Methods**		
**Participants**	Eligibility criteria for participants and the settings where the data were collected	Eligibility criteria for general practices:
		Location within the Leiden - the Hague region. General practitioner/practice nurse that is willing and available to support patients in internet-based self-management.
		Patient eligibility criteria: Age 18 to 50 years; a doctor diagnosis of asthma; prescription of inhaled corticosteroids and/or montelukast ≥ three months within 12 months prior to enrolment; internet access; ability to understand written and oral Dutch instructions. Patient exclusion criteria: Severe co-morbidities, daily or alternate day oral corticosteroid therapy for ≥1 month prior to entering the study and being primarily under treatment by a respiratory physician.
		Data will be collected in a research module of the internet-based self-management support program (PatientCoach.nl) using web-based questionnaires (SurveyGizmo, Boulder, Colorado).
**Interventions**	Interventions intended for each group	Internet-Based Self-Management (IBSM) support program :
		PatientCoach.nl consists of both a generic web-based system and an instruction visit for patients. PatientCoach includes modules for self-monitoring (asthma control and lung function), a treatment plan (medication,), motivational feedback, e-consultation, personalized information (i.e., inhalation technique), reminders and forums for patients and professionals. PatientCoach has been developed by the LUMC. Patient Coach will be integrated in the general practice information system. Additionally PatientCoach contains a research module which consists of electronic versions of questionnaires.
		General practice level
		The implementation strategies for internet-based self-management support are primarily targeted general practices:
		1. Minimum strategy (MS): dissemination of the IBSM program.
		2. Intermediate strategy (IS): MS + start-up support for professionals (i.e., support in selection of the appropriate population and training of professionals).
		3. Extended strategy (ES): IS + additional training and ongoing support for professionals.
		All general practices will be asked to invite at least 10 patients to participate in PatientCoach. Follow-up duration at general practice level is one year.
		Patient level:
		Instruction visit on how to use PatientCoach, particularly focusing the essential self-management skills in asthma (i.e., monitoring, inhalation technique). Patients will be instructed to monitor their level of asthma control at least once per month, preferably once weekly using the Asthma Control Questionnaire. General practices themselves can decide whether the practice nurse and/or general practitioner guide patients in using PatientCoach. Follow-up per patient is six months. However, patients will have the possibility to continue using PatientCoach.nl after this period.
**Objective**	Specific objective or hypothesis	The objectives of this study are to investigate the effectiveness and cost- effectiveness of a Minimum strategy, as compared to an Intermediate strategy and an Extended strategy in a three arm cluster-randomized trial. Since these different implementation strategies have a sequence of effects, the evaluation is aimed to assess to what extent: 1. practices participate in IBSM (practice level); 2. IBSM improves asthma related quality of life (patient level); 3. patients participate in IBSM (patient level); and 4. The various implementation strategies are cost-effective (societal/organisational level)
**Outcome**	Clearly defined primary outcome for this report	Primary outcome measures are a) the proportion of referred patients that participate in IBSM (general practice (cluster) and patient level) and b) the proportion of patients that have clinically relevant improvement in the asthma-related quality of life as measured by the Asthma Quality of Life Questionnaire [30].Patient usage of IBSM is defined as two out of three months ACQ-monitoring compliance.
**Randomisation**	How participants were allocated to interventions	As the implementation strategies (interventions) are primarily targeted at general practices, randomisation will occur at practice level.
		General practices (i.e., 2,300 patients per ‘standard practice’) are the unit of randomisation. Prior to informed consent all general practices in the Leiden-the Hague region will be allocated to one of the three strategies (1:1:1 ratio). General practices receive a letter with information on the allocated strategy and an invitation to participate in the project.
		Randomization will be conducted by [name] using a computer-generated, permuted-block scheme. Practices will be stratified according the following characteristics: postal code (area) and practice size (practices with < 4 general practitioners are defined as a small practice, practices with ≥4 general practitioners as a large practice.
		General practices will be enrolled by [name], [name] and [name]. Patients will be enrolled by general practices.
**Blinding (masking)**	**Whether or not participants, care givers, and those assessing the outcomes were blinded to group assignment**	All general practices and patients are blinded to group allocation. Researchers are not blinded for group allocation.
